### Data Collection and Management

Data are entered into a pseudonymized, access-controlled database on secure hospital servers with routine quality checks (double-entry for a 10% sample and discrepancy resolution from source forms). Each participant is assigned a study ID; no names or identifying information are entered in the analytic dataset. The patient questionnaires (FAPI, HCCQ, and self-rated understanding) are filled by the patient in a private area after their visit, with research staff available to assist if needed (for example, reading questions aloud if the patient has minor reading difficulties; severe impairment was an exclusion criterion). The physician questionnaire (DDPRQ-10) is filled separately by the physician immediately after the visit, without seeing the patient’s responses. Consultation time is recorded in minutes by staff. Any technical issues (eg, the AI summary not being ready in time) are documented, and those patients are analyzed in their assigned group according to the intention-to-treat principle.

Data management will follow Good Clinical Practice guidelines. Regular data quality checks will be performed, and any discrepancies in entry will be corrected by checking against the source paper. The analysis will primarily be intention-to-treat, including all randomized patients in the groups to which they were assigned. If any patient does not receive the intervention (eg, technical failure to generate the summary) or does not complete outcomes, this will be noted; missing data will be handled through multiple imputation if less than 5% are missing, or through sensitivity analyses excluding those cases.

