### Sample Size and Power Calculation

We determined the target sample size of 300 patients per trial (150 per arm) through power analysis based on the primary outcome (FAPI score). From previous studies using the FAPI/QQPPI in similar settings, we estimate the mean (SD) FAPI score in usual care to be approximately 3.5 (SD 1.0) on the 5-point scale. We consider an increase of 0.3-0.5 in the mean score (with 0.5 being a medium effect, roughly half an SD) to be a clinically important improvement in communication quality. To detect a difference of 0.5 with 80% power at a 2-sided α of 0.05 using a 2-sample *t* test (2-tailed), approximately 63 patients per group are required. To be conservative and account for potential dropout or non-evaluable responses (eg, incomplete questionnaires), we inflated the sample. Our goal of 300 participants per trial (150 per arm) provides >90% power to detect an effect size of *d*=0.5 and approximately 80% power to detect a smaller effect of *d*≈0.4. This sample also provides ample power (>80%) for detecting differences in secondary outcomes, such as a 10-point difference in the 0-100 scaled DDPRQ-10 or approximately a 1-point difference in the understanding rating. We do not plan an interim efficacy analysis, but an internal check of assumptions, such as variance, will be conducted after approximately 50% enrollment to ensure the sample size remains adequate. Given the consecutive recruitment strategy, we anticipate reaching 300 patients in each trial within the planned 6-month recruitment window, as the neurosurgery service sees dozens of new patients weekly and discharges dozens monthly, with a good proportion expected to consent.

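### The missing-data threshold runs the wrong way: imputation below 5% missing, and at 5% or more only exclusion, so no stated primary method keeps all randomized patients

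*Protocol article*

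**What the plan says.** The second paragraph of Data Collection and Management sets the analysis population: "The analysis will primarily be intention-to-treat, including all randomized patients in the groups to which they were assigned". It then turns to patients who do not get the summary or who leave outcomes incomplete. It says of a patient who has no summary "or does not complete outcomes, this will be noted", and closes with the rule that "missing data will be handled through multiple imputation if less than 5% are missing, or through sensitivity analyses excluding those cases".

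The first paragraph of the same section keeps patients whose summary was not ready in their assigned group.

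Nothing else in the article gives a missing-data method. Statistical Analysis Plan and Secondary Outcomes Analyses name the tests only. Sample Size and Power Calculation mentions loss as one reason for the larger sample ("account for potential dropout or non-evaluable responses (eg, incomplete questionnaires), we inflated the sample") but gives no rate.

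**The concern.** The rule ties the method to the amount of missing data in the wrong direction. When few scores are missing, imputing or omitting them gives nearly the same answer. As the share grows, so does the room for non-response to distort the comparison, and this is where the rule stops imputing and mentions only leaving patients out.

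A comparison of completers is not a comparison of everyone randomized. Nor is a sensitivity analysis a primary analysis, so on the literal wording nothing primary is defined from 5% upward.

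This bears on the primary outcome of both trials. Patients know their arm and rate their own doctor, and there is a single assessment with no follow-up. A missing FAPI score cannot be supported by a later one, and no baseline FAPI is planned. Under No Blinding and Potential Bias, the article itself accepts that knowing the arm may colour patients' ratings. Non-response that differs by arm is therefore plausible, though the documents do not show it.

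**Working it through.** **1. The plan's own figure.** Inputs from Sample Size and Power Calculation: "To detect a difference of 0.5 with 80% power at a 2-sided α of 0.05", with a usual-care score of "approximately 3.5 (SD 1.0) on the 5-point scale".

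n per arm = 2 × (1.960 + 0.842)² × 1.0² / 0.5² = 62.8, so 63. This agrees with "approximately 63 patients per group are required". The exact t-test calculation gives 63.8, so 64. The 5% threshold is a decision rule with no derivation to reproduce.

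**2. Where the rule switches.** 0.05 × 300 = 15 patients per trial, taking the percentage over all randomized patients in a trial. The article does not say which denominator applies.

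**3. What each reading gives at 5% or more.**
- The exclusion is the primary analysis: it is complete-case and omits randomized patients.
- The exclusion is only a sensitivity analysis: no primary handling is stated.
- The excluded cases also include patients who received no summary, since the sentence covers both groups: this contradicts the section's first paragraph, which keeps such patients in their assigned group.

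**4. Size of the possible bias.** Let m be the share missing in an arm and g the number of points by which non-responders score below responders, taken as equal in both arms. Completers overstate an arm's mean by m × g, so

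bias of the difference (intervention minus control) = (m_intervention − m_control) × g.

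Neither m nor g is in the documents. Both are assumptions, with g from 0.5 to 1.0.

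| Missing, intervention | Missing, control | Bias at g = 0.5 | Bias at g = 1.0 |
|---|---|---|---|
| 10% | 20% | −0.05 | −0.10 |
| 20% | 10% | +0.05 | +0.10 |
| 5% | 10% | −0.025 | −0.05 |
| 10% | 10% | 0 | 0 |

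The article calls 0.3 to 0.5 points clinically important. A bias of 0.10 is 0.10 / 0.3, one third of the lower bound, or 0.10 / 0.4, one quarter of a 0.4-point effect.

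If only one arm loses patients, the bias is 0.025 to 0.05 at 5% missing in that arm, 0.05 to 0.10 at 10%, 0.075 to 0.15 at 15% and 0.10 to 0.20 at 20%. The exposure thus grows across the range in which the rule no longer imputes.

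**5. Power is not the issue.** With equal exclusion in both arms, two-sided t-test power at d = 0.4 is:

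| Missing | Per arm | Power |
|---|---|---|
| 0% | 150 | 93.2% |
| 5% | 142 | 91.9% |
| 10% | 135 | 90.6% |
| 15% | 128 | 89.0% |
| 20% | 120 | 87.0% |

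The article's own figure of about 80% at d ≈ 0.4 is a separate matter.

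**The case against.** **The wording is loose, and complete-case is only one reading.** This stands. A reader might infer that the protocol commits to a complete-case primary analysis at 5% or more. It does not say so; it calls the exclusion a sensitivity analysis. The supportable statement is that the primary analysis there is complete-case or undefined, and the promise of all randomized patients fails either way.

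**The threshold may never be reached.** This also stands. Forms are completed straight after the consultation, patients must be able to complete a short survey, and staff help with the questionnaires. A reader might infer from the inflated sample that the plan expects substantial loss, but the article speaks only of potential dropout and names no rate. Some loss remains possible: patients may withdraw, and inpatients fill in the form on the day of discharge.

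**The bias figures are assumed, and their direction is open.** Correct. If dissatisfied patients go missing mainly from control, the complete-case difference is too small and works against the intervention. The opposite imbalance would inflate it.

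**Imputation would not recover the quoted bias.** Largely correct. If dissatisfied patients skip the form, missingness depends on the unseen score. There is no baseline FAPI, and HCCQ and self-rated understanding come from the same patient in the same sitting, so they will often be missing too. Only the delta-adjusted analysis addresses that mechanism.

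**An article leaves such detail to the analysis plan.** True of the imputation model's details, but not of this point. The article states a rule, and the rule runs the wrong way.

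**Conclusion.** The point holds as a defect in a stated rule. Imputation is confined to the range where it matters least, and from about 15 missing patients per trial no method is named that retains everyone randomized. This conflicts with the intention-to-treat commitment in the same paragraph.

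The consequence is conditional. It requires at least 5% missing, non-response related to the score, and different losses between arms (or a different responder gap, which the formula above holds equal). None of these is documented. On the assumed values of 10% against 20% missing and a gap of 0.5 to 1.0 points, the shift is 0.05 to 0.10 points, in either direction. The documents do not support saying that bias will occur, that it would favour the intervention, or that imputation by itself would remove it.

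Because the rule governs the primary outcome in both trials, it should be settled before anyone sees outcome data by arm.

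**What to change.** - Delete the 5% switch and name one primary method for every level of missingness: multiple imputation covering all randomized patients in their assigned arms. Use the baseline variables (age, sex, education), clinician, DDPRQ-10 and consultation time, plus HCCQ and self-rated understanding where available. DDPRQ-10 and consultation time are recorded by the physician and staff, so they can exist when the patient's form does not.
- Report complete cases only as a sensitivity analysis.
- Add a delta-adjusted sensitivity analysis in which missing FAPI scores are set lower than imputed, varied separately by arm, to show how large a departure would change the conclusion.
- State that patients who did not receive the summary stay in their assigned group and are not among the cases excluded.
- The Results section says the statistical analysis plans are finalized. If they already contain such a method, it is enough to correct the article's sentence to match.

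The cost is about one sentence of text and light programming. No new data are needed, and neither the sample size nor α changes.

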### Statistical Analysis Plan

We will first describe the sample using summary statistics (means or medians for continuous variables, frequencies for categorical variables). The two trial populations (outpatient vs inpatient) will be described separately. Baseline characteristics will be compared between arms to ensure that randomization achieved balance; any significant differences will be noted and adjusted for in secondary analyses if needed.

For the primary outcome (FAPI score), we will compare the intervention and control group means using an independent-samples *t* test (or nonparametric Wilcoxon rank-sum test if the distribution is highly skewed, although previous studies suggest near-normal distribution). We will report the mean difference with 95% CI. The primary analysis will be carried out separately for each trial. However, since the interventions and outcomes are identical, we may also perform a pooled analysis across both trials to increase power, including an indicator for trial to account for any systematic differences in context. Our hypothesis test is 2-sided with α=0.05. We anticipate a positive difference (intervention > control).

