#### Screening and Recruitment

A study team member (a trained research nurse or physician) will screen upcoming clinic appointments and inpatient lists daily to identify potential participants meeting the above criteria. Recruitment is consecutive, meaning every patient who meets criteria is approached without selection beyond eligibility, to minimize sampling bias. Patients will be provided written and oral information about the study, and written informed consent will be obtained by study personnel prior to randomization. The general nature of the intervention (receiving an AI-prepared explanation) will be explained, but participants will not be explicitly told whether their documents have been simplified by AI until after the consultation (to avoid expectation bias, although patients in the control arm will likely notice the absence of a simplified text). They are told that the study is comparing different ways of providing information.

At the time of consent, baseline data will be collected, including demographics (age, sex, education level) and clinical context (diagnosis, type of document available). No identifiable personal health data beyond what is needed for outcomes will be retained in the research dataset, and all AI processing of documents occurs on secure servers in adherence with privacy regulations (no patient-identifying information is input to the AI model). Participants are free to withdraw at any time. We anticipate high acceptability of the intervention; similar studies have reported that patients appreciate receiving additional explanations [7].

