To mitigate expectancy and performance bias, we use several safeguards: (1) all participants receive a standardized neutral script at enrollment (“You will receive information materials that may vary in format”); (2) clinicians are instructed not to explicitly reference the AI summaries; (3) objective endpoints, such as consultation time, complement self-reported measures; (4) the analyst is blinded to group codes; and (5) sensitivity analyses adjusted for age, education, and clinician identifier will be conducted.

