#### Control (Usual Care)

Participants randomized to the control arm go through usual care procedures without any additional intervention. For outpatients, this means they have whatever documents they normally would (often patients do bring their referral letter or test results, but these are in technical language, and we do not provide any translated version). They will have their consultation with the doctor using those standard materials. For inpatients, usual care means they receive the standard discharge summary at the end of the discharge discussion (or sometimes given to them to hand to their next doctor), but not ahead of time in simplified form. Essentially, the control group represents the status quo: the patient relies on the doctor’s oral explanation during the consultation and on the standard medical documents, with no separate plain-language text.

All other aspects of care are identical between groups. Both groups’ consultations take place with the same pool of physicians (neurosurgery attendings or senior residents), in the same settings. Physicians will have the original medical documents in both cases for reference. After the consultation, both groups complete the outcome questionnaires described below.

Notably, if a patient in the control group expresses strong confusion about their medical documents or requests an explanation in writing, the physician will handle it per usual care (which might involve some oral explanation or writing brief notes, but the prepared AI summary will not be provided at that point, to preserve the integrity of the comparison). However, at the end of the study, control patients will be offered the layperson-friendly summary if they desire, as an ethical consideration to avoid denying potentially helpful information.

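### The primary FAPI test leaves out age, education and clinician, which the protocol already plans to adjust for, and secondary adjustment follows baseline significance tests: a matter of efficiency and prespecification, not of validity

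*Protocol article*

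**What the plan says.** Three statements bear on adjustment, and all refer to the same trials.

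- **Primary test.** The Statistical Analysis Plan section says that for FAPI "we will compare the intervention and control group means using an independent-samples" t test, with a Wilcoxon rank-sum test if the scores are highly skewed. Secondary Outcomes Analyses uses t tests for HCCQ and DDPRQ-10 too.
- **Planned adjusted model.** Randomization and Blinding lists, among its safeguards against bias, that "sensitivity analyses adjusted for age, education, and clinician identifier will be conducted".
- **Baseline rule.** The Statistical Analysis Plan section compares the arms at baseline to see whether randomization produced balance, and says that "any significant differences will be noted and adjusted for in secondary analyses if needed".

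On the covariates, Screening and Recruitment says that "baseline data will be collected, including demographics (age, sex, education level) and clinical context (diagnosis, type of document available") at consent. The clinician is not on that list, although the planned sensitivity analysis implies that an identifier is recorded. Control (Usual Care) says that both groups' "consultations take place with the same pool of physicians (neurosurgery attendings or senior residents), in the same settings"; it does not say how many physicians there are. Randomization and Blinding describes a 1:1 list and mentions no stratification by clinician, age or education.

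**The concern.** FAPI and HCCQ are a patient's ratings of one doctor, and DDPRQ-10 is a doctor's rating of one encounter. Stable differences between doctors, and any relation of the score to age or education, are therefore part of the outcome variance. An unadjusted t test leaves all of that in the error term, although the authors already intend to model it. At stake are the width of the confidence interval and some power at the lower end of the effects that the protocol calls important.

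The baseline rule is a separate weakness. After proper randomization, any baseline difference is due to chance, so a significance test of it cannot show whether randomization worked. Nor does a small P value mark a variable as prognostic. Selecting covariates this way, with the added discretion of adjusting only if needed, fixes the secondary adjusted models after the data are seen. The planned sensitivity model and the baseline rule can also give different adjusted estimates, and the article does not say which one counts.

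**Working it through.** **Inputs from the protocol article.** Sample Size and Power Calculation: usual-care FAPI "approximately 3.5 (SD 1.0) on the 5-point scale"; important difference 0.3 to 0.5 points, so d = 0.3 to 0.5; two-sided alpha 0.05; 150 per arm. Screening and Recruitment: five baseline variables (age, sex, education, diagnosis, document type).

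**Assumed, because the documents do not give it.** The share of FAPI variance explained by age, education and clinician together (R²), shown from 0.05 to 0.20.

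**Step 1: the plan's own figure.** For a difference of 0.5, SD 1.0 and 80% power, the normal approximation gives 63 per group and the exact t calculation 64. The stated 63 reproduces. Unadjusted power at 150 per arm by noncentral t is 73.6% at d=0.3, 93.2% at d=0.4 and 99.1% at d=0.5. The article's figure of about 80% at d≈0.4 is lower than the 93.2% used here; that is a separate matter.

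**Step 2: confidence interval.** The standard error of the difference is SD × √(2/150) = 0.1155 without adjustment, and it is multiplied by √(1−R²) with adjustment.

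- R² 0.05: √0.95 = 0.975, about 2.5% narrower.
- R² 0.20: √0.80 = 0.894, about 10.6% narrower.

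**Step 3: power.** The noncentrality is d/√(1−R²) × √(150/2). At d=0.3 it is 0.3 × 8.660 = 2.598 when R² = 0. Spending 5 to 25 degrees of freedom on covariates changes these analytic figures by less than 0.1 point.

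| R² | Equivalent n per arm, 150/(1−R²) | Power, d=0.3 | Power, d=0.4 |
|---|---|---|---|
| 0 | 150 | 73.6% | 93.2% |
| 0.05 | 158 | 75.7% | 94.3% |
| 0.10 | 167 | 77.9% | 95.3% |
| 0.15 | 176 | 80.2% | 96.3% |
| 0.20 | 188 | 82.5% | 97.1% |

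**Step 4: what the formula leaves out.** It ignores chance imbalance of many clinician indicators between the arms. Simulation with N=300, age, three-level education and clinicians as fixed effects (3,000 runs per cell, Monte Carlo error about 0.8 points), at d=0.3:

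| Total R² | 8 clinicians, unadjusted to adjusted | 15 clinicians, unadjusted to adjusted |
|---|---|---|
| 0 | 73.2% to 72.0% | 71.7% to 69.2% |
| 0.10 | 72.3% to 75.3% | 73.3% to 75.5% |
| 0.20 | 73.7% to 81.2% | 74.8% to 79.9% |

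Break-even R² is roughly covariate parameters/N: (7+3)/300 = 3.3% with 8 clinicians and (14+3)/300 = 5.7% with 15.

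A random intercept for clinician alone (4,000 runs, d=0.3) avoids that loss. At an intraclass correlation of 0, power goes from 73.1% to 73.3% with 8 clinicians and stays at 73.8% with 15. At 0.20, it goes from 75.8% to 82.6% and from 74.4% to 81.1%.

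**Step 5: validity.** Under the null, with fixed clinician effects, simulated type I error was 4.5% to 6.0% unadjusted and 4.7% to 5.7% adjusted. With the random intercept, the adjusted test gave 4.3% to 5.8% and the unadjusted test 4.0% to 5.5%. Both methods stay close to 5%.

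**Step 6: baseline rule.** With five independent tests at 0.05, the chance of at least one significant result under correct randomization is 1 − 0.95⁵ = 22.6%. Correlated variables would change this figure somewhat.

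**The case against.** The strongest reply is that nothing in the primary analysis is wrong. Patients are randomized individually, the same physicians serve both arms, and type I error is held. The design is also consistent with itself, since the trial is powered on a two-sample t test and analysed with one. The adjusted model is committed to whatever the baseline tests show, and the significance rule is confined to secondary analyses. All of this stands. A reader might infer that shared clinicians make the t test invalid, or that chance imbalance decides the primary result; the documents support neither.

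It is also fair that the size of the gain is unknown. At d=0.4 with full recruitment, power is already 93.2%, so the gain is about 1 to 4 points. A reader might infer that adjustment is free. That fails if many clinicians enter as fixed effects and the covariates explain little, where the loss is about 1 to 2.5 points. Nor do the documents support a claim that a few physicians rate most patients, or any particular intraclass correlation for DDPRQ-10.

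The gain would look larger if AI-MEDTALK had only 90 per arm, from 30 inpatients a month over six months. The Results section, however, lets recruitment run to February 2026 or until the target is reached, and allows an extension. That is a question of accrual, not of this analysis choice.

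Lastly, the consultation follows randomization. The clinician actually seen is a clean covariate only if not influenced by arm, and the article does not say how clinicians are assigned. This limits the remedy and is dealt with there.

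**Conclusion.** The point holds as one of efficiency and prespecification. The primary t test is valid but passes over a model that the authors have already chosen. The baseline significance rule is uninformative and makes the secondary adjusted analyses depend on the data; the primary result is unaffected.

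The benefit matters most at d=0.3, the low end of the stated important range, where an R² of about 0.15 would bring power to 80%. At d=0.4 it is small. These sizes rest on the protocol's SD of 1.0, on 150 evaluable patients per arm and on an assumed R² of 0.05 to 0.20. If the covariates explain almost nothing, the gain is near zero. The change is worth making because it needs no extra patients and settles in advance which adjusted estimate counts.

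**What to change.** - **Primary analysis, each trial:** one prespecified linear mixed model for FAPI, with arm, age and education as fixed effects and a random intercept for clinician. Report the adjusted mean difference with its 95% CI.
- **Secondary scores:** the same model for HCCQ and DDPRQ-10.
- **Sensitivity analysis:** the unadjusted t test.
- **Clinician variable:** the clinician scheduled before allocation is revealed, so that arm cannot affect the covariate.
- **Baseline table:** descriptive, without P values. Delete the rule that adjusts for significant differences.

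The amendment should be dated before the group codes are broken.

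**Cost.** Mostly wording. The scheduled clinician must be noted at enrollment, which may be a new data item because the listed baseline data do not include it. Where the scheduled and actual clinicians differ, the model recovers less of the between-clinician variance. The random intercept is preferred because many fixed clinician effects could cost 1 to 2.5 points of power.
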